### Data collection and storage

Data will be collected by LHWs during house visits (screening form), community health workers (during follow-up visits days 1, 7 and 14) and hospital-based study personnel (for all who accept referral and reach hospital premises) on paper forms (online supplemental appendix 3). Given that it will be a new experience for LHWs to assess, classify and manage ARI cases and at the same time record findings on data forms accurately, these will be supervised closely and frequently, at least for the first pneumonia season. Well trained study field supervisory officers and LHW supervisors will be required to perform regular field supervision in their respective clusters and ensure accurate and logically entered data forms and make necessary verifications and corrections at the data collection sites and give feedback to the LHW to avoid repeating the errors. Raw data brought to the programme office will be checked once again for accuracy by the technical staff and approved for entry in the computer. All raw data will be safely kept in the AKU office, appropriately numbered by cluster, until 7 years after the study is over.

#### Case history records

These include the study CRF and HPF that will contain information that documents the child’s eligibility to participate in the study, the signed consent form and information from tests and examinations. Wherever possible copies of supporting documentation for the information contained in the CRF should be kept with each patient’s case history record. This supporting documentation may include records of physical examinations, progress notes, laboratory reports, X-rays, consultations, correspondence, information and data on the subject’s condition, during and after the clinical investigation, diagnoses made, concomitant therapy, etc. All information in the case history records should be attributable to a specific individual. Since the CRF will not contain the patient’s name, there will be a unique link between the ID number on the CRF and the patient’s name. Each child’s case history record will be evaluated to verify validity and completeness of the data on the CRF when a study monitor visits the study site. All corrections to CRF’s must be made without obscuring the original entry. The revised entry should be inserted and the person making the correction should sign and date the correction. Only authorised study personnel may complete or correct CRFs.

### Data management

Screening data will be collected on paper by LHWs. CRF and HPF will be collected on electronic forms. To ensure proper implementation of the intervention, the field supervisors will make spot checks and will arrange monthly refresher group sessions of the first-line health workers in which the problems encountered will be discussed and resolved. In addition, the data collection activity will be carried out by teams consisting of LHWs/CHWs and study staff will be further monitored by field supervisors who will perform a check on a subset (5%) of households.

An information system will be set up to keep track all patients screened and enrolled and a filing system to keep all study related records—case history records, study protocol or related documentation and drug distribution records. The coordinator at the site will be responsible for the completeness and accuracy of all the study materials.

#### Study protocol and related documentation

All study-related documents including the study protocol, manuals of operations, all correspondence sent to or received from the study monitor, materials used for obtaining informed consent, protocol modifications and records of the institutional review board (IRB) approval and all communications with the IRB must be maintained in complete form. These documents will be evaluated to ensure that study documentation is complete and current when a study monitor visits the study site.

#### Record retention

Retention of accurate and complete records is essential to establish the validity and completeness of the study. All records must be retained for 7 years after the data set is frozen. Electronic data will be deidentified, unlinked from any personal identifiers and therefore will protect individual identity.

#### Reporting of serious adverse events and treatment failures

Amoxicillin is in widespread use and is not investigational in any study site. However, since oral amoxicillin is not routinely recommended for initial treatment of children who have severe pneumonia, the appropriate case report forms (CRFs) describing the occurrence of a serious adverse event, treatment failure or death must be faxed to the coordinating centre within 72 hours of the site coordinator knowing about the event. Adverse events, treatment failure and death must be reported to allow appropriate interpretation of this critical information. If the outcome of the adverse event is unknown when the site coordinator first notifies the coordinating centre, a follow-up form must be faxed to the coordinating centre within 10 days of knowing about the event. The PI should send a copy of the adverse event data to their local IRB as soon as possible. The coordinating centre will summarise the adverse event and death information and send a report to the IRB/ERC of sponsors and to site IRBs. Both the rate of adverse events and the rate of patient accrual at each individual site will be monitored to determine if stopping rules are met. We do not anticipate serious adverse events. However, in case of one, a DSMB will be requested for and convened on ad hoc basis for safety review at any time during the study if there is a concern regarding rates of adverse events or rates of patient accrual. Adverse events will be reported by the study physician to the PI and clinically managed by the study physician in conjunction with other physicians at the institution. Any related and unexpected life-threatening adverse event including death will be reported to the IRB within two business days as per IRB protocol and any related, unexpected and serious adverse event will be reported to the IRB within 10 business days as per IRB protocol.

#### Compliance with and deviations from the study protocol

The site coordinator must agree with and sign the protocol and confirm in writing that he or she has read, understands and will work according to the protocol and Good Clinical Practice. The site coordinator is responsible for making sure that the protocol is strictly followed and should not make any changes to the study unless necessary to eliminate an apparent immediate hazard or damage to a trial subject. Any deviations from the study protocol including but not limited to inappropriate enrolment of a study subject, administration of the wrong study treatment, missed doses of study treatment, missed observation points, incorrect administration of concomitant medications, etc should be reported to the coordinating centre and each site’s IRB. The report should include a plan to rectify any problems at the site that may have caused the protocol deviation.

### Sample size

Defining a cluster as (the catchment area of) one LHW, and assuming a power of 90% in detecting 50% increase in referral acceptance from a 10% baseline to 15% among children aged 0–59 months with severe pneumonia (pneumonia prevalence at 2-week recall (MICS Sindh): 7.5% (18% of which is assumed severe pneumonia) with ICC 0.001736. We need to capture a total of 4160 children with severe pneumonia in both intervention and control groups.

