## Introduction

Pneumonia accounts for an estimated 18% of under 5 mortality across the globe.^1^ Majority of these pneumonia-specific deaths occur in 15 countries, in which Pakistan ranks fifth.^2^ Failure to seek early care and delays in hospital referral are commonly acknowledged determinants of mortality in childhood pneumonia with a higher proportion reported from rural settings than urban.^3–6^ Acceptance rates of ‘facilitated’ hospital referral advice have been reported low between 8% and 23% for sick young infants in periurban Karachi.^7 8^ They are even lower for non-facilitated referral in rural settings in children under 5 with severe pneumonia in rural Matiari district, Sindh.^5^ The prominent reasons in low-income and middle-income countries behind this delay are inability to recognise seriousness of pneumonia, distance from health facility and lack of money for private healthcare.^9 10^

In 1994, the government of Pakistan introduced the Lady Health Worker (LHW) programme in rural populations with low physician density to address common health problems in women and children under 5 through household visits. To date, a team of over 110 000 LHWs are working for the programme nationwide with 23 185 LHWs in Sindh alone.^11^ Each LHW is responsible for a population of 1000–1500 individuals (catchment of about 100 families). Recruits are preferably local, with a minimum of 8 years of formal schooling, followed by 15 months of training to deliver maternal and child healthcare (MCH) in community settings. During a monthly home visit, the LHW provides essential MCH services including family planning needs, nutritional assessments of both mother and child, management of minor and common illnesses, improving immunisation coverage and imparting health education.^12^

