### Randomisation and masking

Study clusters were defined as the area covered by an LHW. Each LHW covers a minimum of 100 households. A list of LHWs working in Kotri was collected from the LHW programme, health department government of Sindh. There are a total of 188 active LHWs in the study site. A baseline survey was conducted to collect data on health indicators from the LHW catchments. The clusters were randomly allocated to intervention and control groups on 1:1 fashion with a computer-generated randomisation sequence that was generated by an independent expert. Clusters were matched on under 5 population and distance to referral health facility. No stratification was used for allocation; clusters were selected to ensure that the reporting and training centres of intervention and control LHWs were separate. The investigators and the national and provincial LHW programme coordinators will be excluded from the allocation process.

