### Data analysis

The primary analysis for each outcome will perform on an ‘intention-to-treat’ basis, that is, all children included in the analysis who were enrolled in the study according to the group to which they were allocated. All analyses will account for the cluster randomised design to ensure correct type I error rates and CIs.^35^ Baseline characteristics will be compared by analysing differences in means and proportions among the study arms. Categorical outcomes will be compared using χ^2^ test and continuous outcomes using Student’s t-test. For analysis of predictors of referral acceptance, generalised linear model will be used with logit link function. The univariate analysis will be conducted to explore the independent effect of each predictor on outcome. The variables significant at a liberal p<0.20 will be included in multivariate model for adjustment. The results will be reported as relative risk with 95% CI. Type 1 error will be set at 5% level. All analysis will be done using STATA V.15.

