### Study status

Recruitment began in August 2019 and field activities and data collection are in process. As of 16 October 2020, a total of 235 cases and 184 controls have been enrolled. Extension of study duration is in discussion to achieve sample size.

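### The sample size of 4160 does not follow from its printed inputs, which give about 1,900; the total and inputs must be reconciled before the extension is fixed

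*Protocol article*

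**What the plan says.** The Sample size section takes one LHW's catchment as the cluster and gives these planning values: power, "assuming a power of 90" (per cent); effect, "detecting 50% increase in referral acceptance from a 10% baseline to 15" (per cent); clustering, "with ICC 0.001736". It then concludes: "We need to capture a total of 4160 children with severe pneumonia in both intervention and control groups". It prints no cluster size, design effect or attrition allowance.

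The other inputs are elsewhere in the article. Data analysis: "Type 1 error will be set at 5% level". Randomisation and masking: "There are a total of 188 active LHWs in the study site", with 1:1 allocation of clusters. Study status reports 235 and 184 children enrolled by 16 October 2020 and adds: "Extension of study duration is in discussion to achieve sample size".

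**The concern.** Effect, power, ICC and total are printed together, so the total can be checked against the rest. An ICC of 0.001736 is very small. With 188 clusters it barely inflates an individually randomised design, yet 4160 is more than twice what such a design needs for 10% against 15%.

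Two things depend on this. The stated 90% power is not the power of 4160 children under the stated assumptions. And the length of the extension is being set against 4160. If the inputs are right, the trial would recruit well over 2,000 children more than its stated power requires. If the total is right, a published planning value is wrong by a wide margin.

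**Working it through.** **Inputs.** From the article: p0 = 0.10, p1 = 0.15, power 90%, ICC (ρ) = 0.001736, one LHW area per cluster, alpha 5%, 188 active LHWs, 1:1. Assumed: two-sided test (in line with the planned 95% CI), all 188 areas used (94 per arm), equal cluster sizes.

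**1. Without clustering.** Mean proportion 0.125.
n per arm = [1.960·√(2·0.125·0.875) + 1.2816·√(0.10·0.90 + 0.15·0.85)]² / 0.05²
= (0.9167 + 0.5977)² / 0.0025 ≈ 918.
The total is 1,836. With continuity correction it is 957 per arm, or 1,914.

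**2. With clustering.** Cluster size at the stated total: m = 4160/188 = 22.1.
Design effect = 1 + (22.1 − 1)·0.001736 = 1.037.
Total = 1,836 × 1.037 ≈ 1,903, or 1,984 with continuity correction.

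**3. Other formulas, 188 clusters.**
- Clusters fixed at 94 per arm: 918·(1 − ρ)/(1 − 918ρ/94) ≈ 932 per arm, total 1,864.
- Hayes–Bennett, with the between-cluster coefficient of variation implied by the ICC, √(0.001736·0.90/0.10) = 0.125: total 1,891 unmatched, 1,912 matched.
- Cluster sizes varying with a coefficient of variation of 0.5 to 1.0: total 1,921 to 1,974.

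The plan's 4160 is not reproduced. The ratio 4160/1,903 is 2.19 (2.10 against 1,984).

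**4. Can an unprinted quantity close the gap?**
- *Cluster size.* The design effect needed is 4160/1,836 = 2.27. At ρ = 0.001736 this requires m = 1 + 1.266/0.001736 ≈ 730 severe cases per cluster, which is fewer than 6 clusters in all (4160/730 = 5.7). The Introduction gives each LHW 1000–1500 people of all ages. Taking the plan's prevalence (7.5% × 18% = 1.35%), an assumed under-5 share of 13–17%, and 21 monthly or 45.5 two-weekly rounds, a cluster yields about 37 to 157 cases. The total is then 1,950 to 2,332 (at most 2,431 with continuity correction).
- *Fewer clusters.* 40 per arm gives 1,909; 20 gives 1,992; 10 gives 2,180; 5 gives 2,690; 3 gives 3,910.
- *Attrition.* Dividing by 0.80 for 20% loss gives about 2,380 (2,481 with continuity correction). Reaching 4160 needs 1 − 1,903/4160 ≈ 54% loss.
- *Error rates at m = 22.1.* One-sided 5% gives 1,551. Two-sided with 95% power gives 2,353.

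**5. What 4160 delivers on the printed inputs.** Effective size per arm = 2,080/1.037 ≈ 2,006. Power for 10% against 15% is 99.8%. Power reaches 90% at 10% against about 13.3%.

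**6. Inputs that would give 4160.**
- ICC = 1.266/(22.1 − 1) ≈ 0.06 with 188 clusters. Power at 4160 is then 90.0%.
- A change in the rates: 5% against 7.5% at the printed ICC needs 1,969 per arm, and 2 × 1,969 × 1.037 ≈ 4,080, close to but not exactly 4160. This is an illustration; the article does not give 5%.

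**The case against.** A reader might infer that the extension is chasing a target more than twice too large. The article does not support that. It would follow only if every printed input is the true planning value and the total alone is wrong. If the ICC was really about 0.06, then 4160 is correct and the ICC is understated about 35-fold (0.06/0.001736). Cutting to 1,900 would then be harmful: at 188 clusters m = 10.1, the design effect is 1 + 9.1·0.06 = 1.55, and power for 10% against 15% falls to about 76%. The baseline is open to doubt too, since after quoting 8% to 23% for facilitated referral the Introduction says: "They are even lower for non-facilitated referral in rural settings". That raises a possibility and settles nothing.

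It is also fair to say that an article may leave cluster size, design effect and attrition to the full protocol, so their absence is no fault. Some allowance is plausible, because the Participant section excludes children unavailable on days 7 and 14. But step 4 shows that no ordinary value of these quantities reconciles the printed figures.

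The number of clusters actually randomised is not stated. Clusters were chosen so that training and reporting centres stayed separate, and Limitations says some union councils were left out. Both the 1,900 and the 0.06 depend on 188. Fewer clusters would move them, but nothing short of a handful per arm brings the total near 4160.

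Finally, an extension is needed either way: the 419 children enrolled are about 22% of 1,900 and 10% of 4160. The discrepancy affects how long it must be. If the printed inputs are right, the trial is overpowered; its type I error is unharmed.

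**Conclusion.** The Sample size section is wrong as written: its total and its inputs cannot all be right unless a large inflation was applied and not reported. On the printed inputs the requirement is about 1,900 children (1,860 to 1,985 over formula variants with 188 clusters), and below about 2,350 for any plausible cluster size without continuity correction. The power of 4160 on those inputs is about 99.8%, not 90%. This rests on a two-sided 5% test, all 188 LHW areas in use and roughly equal cluster sizes; relaxing any of these does not rescue the figure.

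Which number is at fault is not shown. The finding is an unreconciled calculation behind a live decision. It does not establish that the target is too large.

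**What to change.** Before the extension is set, go back to the planning calculation and restate the Sample size section so that total, power, sidedness, ICC, number and size of clusters, design effect and any attrition allowance agree.

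- If the printed inputs are the true planning values, restate the required total as about 1,900 to 2,000, or keep 4160 and state its power as over 99%.
- If 4160 is the intended total, correct the ICC, the baseline rate or the inflation on which it rests.

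Do not lower the target until the inputs are verified. The children enrolled so far cannot settle the ICC: 419 over 188 clusters is about 2.2 each, and the large-sample standard error of an ICC at that size is about 0.063, too wide to tell 0.0017 from 0.06.

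The cost is a recalculation and a one-paragraph amendment. The downside is that a published figure changes.

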### Data analysis

The primary analysis for each outcome will perform on an ‘intention-to-treat’ basis, that is, all children included in the analysis who were enrolled in the study according to the group to which they were allocated. All analyses will account for the cluster randomised design to ensure correct type I error rates and CIs.^35^ Baseline characteristics will be compared by analysing differences in means and proportions among the study arms. Categorical outcomes will be compared using χ^2^ test and continuous outcomes using Student’s t-test. For analysis of predictors of referral acceptance, generalised linear model will be used with logit link function. The univariate analysis will be conducted to explore the independent effect of each predictor on outcome. The variables significant at a liberal p<0.20 will be included in multivariate model for adjustment. The results will be reported as relative risk with 95% CI. Type 1 error will be set at 5% level. All analysis will be done using STATA V.15.

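### The predictor model is given a logit link, yet its results are promised as relative risks with no step to obtain them; odds ratios labelled as relative risks would lie further from 1

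*Protocol article*

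**What the plan says.** The Data analysis section of the protocol article names one regression model: "For analysis of predictors of referral acceptance, generalised linear model will be used with logit link function". It describes univariate fits followed by a multivariable fit: "The variables significant at a liberal p<0.20 will be included in multivariate model for adjustment". The next sentence sets the effect measure: "The results will be reported as relative risk with 95% CI".

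Two other sentences in that section bear on scope. Outcomes are given simple tests: "Categorical outcomes will be compared using χ^2^ test and continuous outcomes using Student’s t-test". Clustering is covered by a general commitment: "All analyses will account for the cluster randomised design to ensure correct type I error rates and CIs".

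Under Study aims and design, identifying demographic and clinical predictors of acceptance is one of the primary objectives, and the description of the primary outcome repeats it. The Sample size section is framed as a relative increase: "detecting 50% increase in referral acceptance from a 10% baseline to 15" per cent.

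**The concern.** A logit link models the log odds, so an exponentiated coefficient and its confidence limits are an odds ratio and its limits. A relative risk comes either from a different link or from a further calculation on the fitted probabilities. The article fixes both the link and the reported measure and gives nothing to connect them. An analyst following the text literally would exponentiate the logit coefficients and head the column relative risk.

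The odds ratio is always further from 1 than the relative risk unless the effect is null, and the gap widens as the outcome becomes more common and the effect stronger. At stake are the size of the predictor effects and their intervals, under a primary objective. Mislabelled figures also could not be set beside the 50% relative increase used for planning.

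**Working it through.** **Inputs**
- Link and reported measure: Data analysis section.
- Planned acceptance of 10% and 15%, and total sample size 4160: Sample size section.
- Cited acceptance of 8% to 23%: Introduction, for facilitated referral of sick young infants in periurban Karachi. The Introduction says non-facilitated rural acceptance is lower still.

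**Formulas**, with p0 and p1 the two acceptance probabilities:
- RR = p1 / p0
- OR = [p1 / (1 − p1)] / [p0 / (1 − p0)]

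**Step 1: the plan's own effect.** RR = 0.15 / 0.10 = 1.50, which reproduces the stated 50% increase.

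**Step 2: the same effect on the logit scale.** OR = (0.15 / 0.85) / (0.10 / 0.90) = 0.1765 / 0.1111 = 1.588. The ratio is 1.588 / 1.500 = 1.059, or 5.9% too large. The excess over 1 is 0.588 instead of 0.500, or 17.6% too large.

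**Step 3: other baselines and effects.**

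| p0 | p1 | True RR | OR | OR / RR |
|---|---|---|---|---|
| 8% | 12% | 1.50 | 1.568 | 1.045 |
| 10% | 15% | 1.50 | 1.588 | 1.059 |
| 23% | 34.5% | 1.50 | 1.763 | 1.176 |
| 10% | 20% | 2.00 | 2.250 | 1.125 |
| 10% | 6.67% | 0.667 | 0.643 | 0.964 |
| 10% | 10% | 1.00 | 1.000 | 1.000 |

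The RR of 2.00 is an illustration of a stronger predictor; the article gives no expected predictor effects. The row with RR 0.667 shows that the shift is also away from 1 for factors that lower acceptance.

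**Step 4: effect on the interval.** Take 4160 / 2 = 2080 children in each of two equal groups, with 208 and 312 acceptances (10% and 15%). Fitted without allowance for clustering:
- exponentiated logit coefficient: 1.588 (95% CI 1.317 to 1.915);
- log link: 1.500 (95% CI 1.272 to 1.768);
- the same logit fit followed by marginal standardisation (mean predicted probability with the factor present, divided by the mean with it absent): 1.500.

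Both confidence limits move outward with the odds ratio. The last line shows that a logit fit can give the correct relative risk, provided the extra step is taken. The total of 4160 serves only to set the group sizes here; whether it follows from the stated inputs is a separate question on which this point does not depend.

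**The case against.** The strongest reply is that a logit link and a relative risk are compatible. Marginal standardisation after a logit fit returns a valid relative risk, as Step 4 shows, and nowhere does the article say that exponentiated coefficients will be called relative risks. A condensed article may leave that derivation to an analysis plan. This stands in part: overstatement is conditional on mislabelling. It does not dispose of the point, because the article is not silent. It states a link and a measure that do not correspond, and on a literal reading the label is wrong.

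A second reply concerns size. At the planned rates the gap is 1.59 against 1.50. The 23% end of the cited range is for facilitated referral, whereas this trial uses non-facilitated referral in a predominantly rural district, where the Introduction expects lower acceptance. A null effect stays null, so mislabelling would not create a false positive. All of this stands and limits the severity.

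A reader might infer that every reported effect, including the headline comparison between arms, would be overstated. The documents do not support that. The logit model is tied to predictors; categorical outcomes go to a chi-squared test, and the Abstract mentions analysis of variance for referral acceptance. A reader might also assume much higher acceptance, and so a larger distortion, from the care-seeking figure above 80% in the Trial setting section. That figure concerns care seeking for acute respiratory infection and diarrhoea, not acceptance of hospital referral for severe pneumonia, and cannot serve as a baseline here.

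**Conclusion.** The point holds for the predictor analysis: "generalised linear model will be used with logit link function" and the promised relative risks do not match as written, and no step joins them. If exponentiated coefficients were reported under that label, a true relative risk of 1.50 would appear as 1.59 at the planned 10% and 15%, as 1.57 from an 8% baseline, and as 1.76 from a 23% baseline, which is probably above what this setting would show.

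These figures assume a single two-level predictor. In an adjusted model the gap depends on the acceptance level across covariates, so no single factor corrects it.

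It is unclear whether the relative-risk sentence also covers the comparison between arms. If it does, no estimator is named for that relative risk, since a chi-squared test supplies none; that is an ambiguity to settle, not evidence of an overstated trial result. Severity is moderate: the mismatch affects a primary objective, but it is conditional, modest at the planned rates and easily repaired.

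**What to change.** Amend the Data analysis section in one of two ways.

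1. Replace the logit link with a log link (log-binomial model), falling back to Poisson regression if the model does not converge, with cluster-robust variance at the level of the Lady Health Worker's catchment. Report the exponentiated coefficients as relative risks.
2. Keep the logit link and report odds ratios labelled as such, with risk ratios by marginal standardisation and cluster-robust confidence intervals alongside.

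In either case, state whether the relative-risk sentence also covers the comparison between arms. If it does, name the same estimator for it.

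The cost is one or two sentences. No change to data collection, sample size or conduct is needed, and the methods are available in the software the article names. Enrolment was still under way at the status the article reports, so the choice could be fixed before the outcome data are analysed.
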